### Participants

Participants are eligible if: they are community-dwelling aged 60 years or above and perceive their health as fair or poor. Screening on self-rated health will be performed through the first item of the SF-36 questionnaire: “In general, would you say your health is: (1) Excellent, (2) Very Good, (3) Good, (4) Fair or (5) Poor”.

Participants will be excluded if: they need help to go to the PCC; have cognitive impairment or diagnosed dementia; have a medical condition that contraindicates physical activity; have any severe mental health problem that hinders participation in a group dynamic; have an end-of-life situation.

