### Sample size

A sample size of 390 participants, randomised to the intervention or the control group of 195 participants, will be needed to detect a clinically relevant benefit in self-perceived health after 3-month intervention. Self-perceived health is dichotomized as good health (including excellent, very good and good) and poor health (including fair and poor). The clinically relevant change has been defined as a 10% increase in the prevalence of participants who consider their health as good. The sample size has been estimated on a statistical power of 80%, a significance level of 95%, and an estimated dropout rate of 20%. A prevalence of 20% of bad self-perceived health in the ESCA 2012 in socio-economic class IVa was considered [32]. The calculations were performed with the “ene 3.0” programme.

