#### Data analysis

Reporting of the results will follow the CONSORT guidelines for randomised controlled trials [33].

First of all, a descriptive analysis will be conducted to characterize the intervention and the control group regarding socio-demographic, health and psychosocial variables.

The efficacy analysis will assess changes in the primary and secondary outcomes between the baseline and 3 months assessments comparing study arms (experimental and control group) with mixed linear models with repeated measures. Linear models will be used to adjust for covariables of interest, specially to correct differences between arms in the baseline characteristics, if applicable.

A diagonal matrix design will be considered for the between-participants covariance matrices (covariance structure for random factors). The between-participants correlations induced by the group delivery of intervention will be taken into account in the models.

Further testing of the study hypotheses will be conducted through covariance analyses, including in the model relevant covariates (age, gender, educational and socioeconomic levels), and effect modifiers. Estimates of effect will be computed for planned subgroups on age, gender, educational and socioeconomic levels and will be interpreted with caution as exploratory rather than definitive results.

It will follow the intention-to-treat principle, thus including all randomized participants with a baseline assessment regardless of their permanence in the study or their loss to follow-up, withdrawal or drop-out. Furthermore, sensitivity analyses will be conducted. In the first place, a ‘per protocol’ analysis will comprise all participants with no protocol violations and complete data in the measurements of the primary variables at baseline, end of treatment and follow-up. In a second sensitivity analysis, primary variables with a substantial number of missing values (higher than 5%) will be imputed.

All statistical analyses will use two-sided tests of statistical significance; estimates of the size of treatment effects will be presented with confidence intervals and significance tests. Significance levels will be set to a 5% level, applying the Bonferroni correction to adjust for type I error criteria. All analyses will be performed with SPSS version 20.

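### The sample size is planned on 80% of people already in good health, but only people in fair or poor health can enter, so the stated 80% power is unsupported and could lie either side of 80%

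*Protocol article*

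**What the plan says.** The Sample size section of the protocol article gives the total and the split: "A sample size of 390 participants, randomised to the intervention or the control group of 195 participants". The target effect is "The clinically relevant change has been defined as a 10% increase in the prevalence of participants who consider their health as good". Power and error rate are given as "The sample size has been estimated on a statistical power of 80%, a significance level of 95"% (evidently 95% confidence, that is, 5% alpha), with 20% dropout. The only rate supplied is the survey one: "A prevalence of 20% of bad self-perceived health in the ESCA 2012 in socio-economic class IVa was considered".

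The Participants section sets eligibility: "they are community-dwelling aged 60 years or above and perceive their health as fair or poor". Screening uses the first SF-36 item. The Primary outcome section takes the outcome from that same item and counts fair and poor as bad, and excellent, very good and good as good.

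The Data analysis section adds: "All statistical analyses will use two-sided tests of statistical significance". It also says that the correlation caused by group delivery will be modelled and that a Bonferroni correction will be applied.

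**The concern.** The planning rate and the entry criterion use the same item and the same cut-point, and they disagree. The calculation assumes that 20% are bad; eligibility makes everyone bad at screening. The survey group is a particular socio-economic class, but it was not selected on self-rated health, so its prevalence does not describe the people enrolled.

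For a binary outcome, the variance of the comparison depends on the proportions in each arm at T1. Here the control proportion is the share of people, all fair or poor at screening, who answer good or better about three months later without the programme. Some will cross that boundary on re-asking. The article neither gives that share nor explains how the survey figure relates to it. At stake is how a non-significant result is read: a reader who trusts the 80% would take it as fairly strong evidence against a 10-point benefit, and whether that is warranted depends on an unstated number.

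**Working it through.** **Inputs from the protocol article.** 195 per arm; power 80%; alpha 5%; dropout 20%; 20% bad, hence 80% good; effect +10 points, hence 90% good (Sample size). Two-sided tests (Data analysis). Entry only if fair or poor on the outcome item (Participants, Primary outcome). Evaluable per arm: 195 × (1 − 0.20) = 156.

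**Formula.** Two independent proportions, pooled variance under the null, with p̄ = (p1 + p2)/2:

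n = [z_α √(2p̄(1 − p̄)) + z_β √(p1(1 − p1) + p2(1 − p2))]² / (p2 − p1)², then n/(1 − 0.20) for dropout.

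**Step 1: reproduce the plan's figure.** With p1 = 0.80, p2 = 0.90, p̄ = 0.85, the two roots are √0.255 = 0.505 and √0.25 = 0.500, and z_β = 0.842.

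- One-sided 5% (z = 1.645): (0.831 + 0.421)²/0.01 = 156.6; with dropout, 156.6/0.80 = 195.8. This matches 195.
- Two-sided 5% (z = 1.960): (0.990 + 0.421)²/0.01 = 199.0; with dropout, 199.0/0.80 = 248.7, or 249 per arm (498 in total). This does not match.
- Two-sided with no dropout allowance gives about 199 (195 with an arcsine formula), but the article says that dropout was included.
- Other readings do not give 195. After dropout, 20% versus 30% good needs 289 one-sided or 368 two-sided; a relative 10% increase (80% versus 88%) needs 324 or 412.

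So the survey figure was the working control rate, and with the stated dropout the calculation appears to have been one-sided.

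**Step 2: power at the plan's own rates, two-sided.** Power = Φ{[0.10√n − z_α √(2p̄(1 − p̄))] / √(p1(1 − p1) + p2(1 − p2))}. With n = 156: (1.249 − 0.990)/0.500 = 0.519, and Φ(0.519) = 0.70.

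**Step 3: power over assumed control rates.** Same formula, n = 156 per arm, +10 points. The article gives no control rate, so these are assumptions.

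| Control good at T1 | Two-sided 5% | One-sided 5% |
|---|---|---|
| 0% | 0.98 | 0.99 |
| 5% | 0.84 | 0.91 |
| 10% | 0.70 | 0.80 |
| 20% | 0.53 | 0.65 |
| 30% | 0.46 | 0.58 |
| 45% | 0.42 | 0.55 |

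Power crosses 80% at a control rate of about 6% two-sided and about 10% one-sided.

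**Step 4: separate the two problems.** The formula is symmetric, so 10% versus 20% needs the same n as 80% versus 90%. In the 10% row, the fall from 0.80 to 0.70 is therefore due to sidedness alone. Reading down a column shows the effect of the control rate; reading across a row shows the effect of sidedness.

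**Limit.** These are powers for independent observations and one test at 5%. The group-delivery correlation and the Bonferroni correction named under Data analysis would both lower them.

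**The case against.** The strongest reply is that the error need not hurt. If few controls improve, power exceeds the claim: 0.98 at a 0% control rate and 0.84 at 5%. If about 10% improve, the symmetry in the formula returns exactly the planned N. This stands, and it rules out a stronger reading: a reader might infer from the lower rows that the trial is underpowered, or probably had less than 50% power. The documents do not support that. Nothing in them makes 30% or 45% more likely than 0% to 6%, and power below one half needs a two-sided test together with a control rate above 20%. On the one-sided basis that reproduces 195, power does not fall below 0.55 at any tabulated rate. Symmetry does not rescue the stated figure either, because the article does not assume a 10% control rate, and at that rate two-sided power is 70%.

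It can also be said that recruitment is complete, that neither the effect estimate nor the type I error is biased, and that the promised confidence intervals will show whether a 10-point benefit is excluded whatever rate was used in planning. All of this is fair and limits the harm. It does not make the power statement correct.

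A third reply is that an article condenses a fuller plan. That would excuse a missing rate. Here a rate is stated, and it conflicts with the article's own entry criterion.

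Finally, the planned analysis is a mixed model with repeated measures, not a two-proportion test. True, but the plan's own N is reproduced by the two-proportion formula, so the figures above are on the plan's footing.

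**Conclusion.** The point holds in this form: the planning prevalence contradicts eligibility on the same item and cut-point, the rate that matters is not stated, and the 80% power is therefore unsupported for the enrolled population. It could be higher or lower. On simple two-proportion power, two-sided, with 156 evaluable per arm and a 10-point effect, it lies between 0.98 and 0.42 for control rates of 0% to 45%, and is below 80% once that rate exceeds about 6%.

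A second, separate inconsistency is that 195 per arm, with the stated dropout, needs a one-sided 5% test, while the analysis is two-sided. Even on the plan's own 80% versus 90%, two-sided power is about 70%.

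These results assume that the 10% increase means percentage points, that dropout is 20% in each arm, that observations are independent and that a single test is made at 5%. The control rates are assumptions, since the article offers none.

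**What to change.** In the Sample size section, replace the survey prevalence with an explicit assumed proportion of controls in good health at T1 among people who were fair or poor at entry. Use the feasibility study to support it if it holds the data; otherwise label it as an assumption. Restate two-sided power, or the detectable difference, at the enrolled N over control rates from 0% to about 45%. Say that group-delivery clustering and the Bonferroni correction are not in those figures and would reduce them, or build them in. State the sidedness and write the significance level as 5%. Delete the unqualified 80% claim.

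This can still be done without knowledge of outcomes: the Trial status section says that everyone has been included but nobody has completed the outcomes assessment. The cost is revised wording and one table, with no extra enrolment. The price is a stated power that may look less favourable than 80%.

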#### Data collection

Data collected during the study period will include a questionnaire completed by a face-to-face interview with a researcher at baseline, post-intervention and follow-up points. The time for completion will be documented. Participants will be contacted by telephone prior to each follow-up point, to arrange a convenient time for completion with the researcher. All patient data will be kept in strict confidence and managed in accordance with the Spanish Data Protection Organic Law 1999. The data will be stored for 5 years after the end of the study. Following completion of the trial, a cleaned anonymised data set will be shared on request. A complete schedule of enrolment, interventions and assessments times is provided on Table 3.

**Table 3 Tab3:**
[figure not shown]
Schedule of enrolment, interventions, and assessments

#### Data analysis

Reporting of the results will follow the CONSORT guidelines for randomised controlled trials [33].

First of all, a descriptive analysis will be conducted to characterize the intervention and the control group regarding socio-demographic, health and psychosocial variables.

The efficacy analysis will assess changes in the primary and secondary outcomes between the baseline and 3 months assessments comparing study arms (experimental and control group) with mixed linear models with repeated measures. Linear models will be used to adjust for covariables of interest, specially to correct differences between arms in the baseline characteristics, if applicable.

A diagonal matrix design will be considered for the between-participants covariance matrices (covariance structure for random factors). The between-participants correlations induced by the group delivery of intervention will be taken into account in the models.

Further testing of the study hypotheses will be conducted through covariance analyses, including in the model relevant covariates (age, gender, educational and socioeconomic levels), and effect modifiers. Estimates of effect will be computed for planned subgroups on age, gender, educational and socioeconomic levels and will be interpreted with caution as exploratory rather than definitive results.

It will follow the intention-to-treat principle, thus including all randomized participants with a baseline assessment regardless of their permanence in the study or their loss to follow-up, withdrawal or drop-out. Furthermore, sensitivity analyses will be conducted. In the first place, a ‘per protocol’ analysis will comprise all participants with no protocol violations and complete data in the measurements of the primary variables at baseline, end of treatment and follow-up. In a second sensitivity analysis, primary variables with a substantial number of missing values (higher than 5%) will be imputed.

All statistical analyses will use two-sided tests of statistical significance; estimates of the size of treatment effects will be presented with confidence intervals and significance tests. Significance levels will be set to a 5% level, applying the Bonferroni correction to adjust for type I error criteria. All analyses will be performed with SPSS version 20.

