### Randomisation and blinding

Participants who sign the informed consent will be scheduled for the baseline assessment. Once the participant has been included in the study, assigned an identification code, and has completed the study baseline assessment, the participant will be randomised to one of the two study groups: intervention and control group (fig. 1). Concealed randomisation will be conducted centrally at FSiE-UAB, using a computer-based random-block randomisation scheme, stratified by PCC. In each PCC, one experimental group and one control group will be set up. Participants and professionals conducting the group-based intervention will remain unblinded, likewise participants can easily reveal their group allocation and thus blinding outcome assessors would be hard to sustain.

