### Primary outcome

The primary outcome of the study is self-perceived health and will be estimated through the first item of the SF-36 questionnaire considering good self-rated health if they answer (1) Excellent, (2) Very Good or (3) Good, and bad self-rated health if they answer (4) Fair or (5) Poor.

For an overview of primary and secondary outcomes, outcomes measures, instruments and assessments time points, see Table 2.

**Table 2 Tab2:** Overview of outcomes, outcome measures, instruments and assessments time points

Outcomes	Outcome (measures)	Instrument	Assessment time points
Personal information	Age, gender, living arrangement, civil status, place of birth, educational background, job, medical conditions	Primary care records Self-report	T_0_
	Changes in living arrangement and civil status		T_1_, T_2_
Primary outcomes	Health status	SF-12 EQ-5D visual analog scale	T_0_, T_1_, T_2_
Secondary outcomes	Quality of life	SF-12	T_0_, T_1_, T_2_
	Social capital	European Values Survey	T_0_, T_1_, T_2_
	Social support	Inventory of social resources in the elderly	T_0_, T_1_, T_2_
	Social participation	Loneliness Este II Scale-Subjective Social Participation Index	T_0_, T_1_, T_2_
	Care and self-care	Self-care semFYC survey Appraisal of Self-Care Agency Scale	T_0_, T_1_, T_2_
	Emotional well-being	Warwick-Edinburgh Mental Wellbeing Scale (WEMWBS)	T_0_, T_1_, T_2_
	Loneliness	Gierveld and De Jong scale Social support perception scale	T_0_, T_1_, T_2_
	Depression	Geriatric depression scale (GDS-5)	T_0_, T_1_, T_2_
	Physical activity	The International Physical Activity Questionnaire (IPAQ)	T_0_, T_1_, T_2_
	Health literacy	Health literacy scale (HLS-EU-16)	T_0_, T_1_, T_2_
	Medication consumption Use of social and health resources	Primary care records Self-report	T_0_, T_1_, T_2_

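### Arms are compared on change from baseline and the outcome's own T0 value is never a named covariate; pre-specifying a common T0 mean or ANCOVA would gain precision on the continuous outcomes at no cost

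*Protocol article*

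**What the plan says.** The Data analysis section states that the efficacy analysis "will assess changes in the primary and secondary outcomes between the baseline and 3 months assessments comparing study arms", to be done "with mixed linear models with repeated measures". It does not say whether the T0 mean is estimated separately in each arm or held equal.

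Two sentences bear on adjustment. The first is "Linear models will be used to adjust for covariables of interest, specially to correct differences between arms in the baseline characteristics, if applicable". The second describes further covariance analyses, "including in the model relevant covariates (age, gender, educational and socioeconomic levels), and effect modifiers". Neither names the T0 value of the outcome being analysed.

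The intention-to-treat set is defined as "including all randomized participants with a baseline assessment regardless of their permanence in the study". Under Randomisation and blinding, allocation follows T0: once the person "has completed the study baseline assessment, the participant will be randomised to one of the two study groups". Table 2 schedules every secondary measure at T0, T1 and T2. It also lists the EQ-5D visual analogue scale, a continuous measure, in the primary row.

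**The concern.** A comparison of mean change between arms subtracts the whole of T0 from T1, so with complete data T0 gets a weight of 1 whatever its correlation with T1. The efficient weight, for equal variances, is rho. Because T0 precedes allocation, the arms share one T0 mean by design, and estimating it separately in each arm discards that knowledge. In a particular sample with a chance T0 imbalance, the change contrast also over-corrects by (1 - rho) times that imbalance. This averages to zero over randomisations, but it adds noise to the one trial that is run.

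The stake is precision on the multi-item scales for self-care, health literacy, social support, loneliness, depressive symptoms and wellbeing. These carry the secondary aims and are to be tested with a Bonferroni correction. The dichotomised self-rated health item is outside this point: eligibility requires fair or poor health, so everyone starts in the same category.

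**Working it through.** **Inputs from the protocol article**
- Arm size, from Sample size: "A sample size of 390 participants, randomised to the intervention or the control group of 195 participants", i.e. 195 per arm.
- Dropout, from Sample size: 20%, so 195 x 0.8 = 156 per arm with T1.
- Intervention groups: one per centre in 16 centres.

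**Inputs that must be assumed.** No T0-T1 correlation, SD or intraclass correlation (ICC) is given for any scale. I take equal SD (set to 1) at T0 and T1, and rho from 0.3 to 0.9. The plan states no precision or power figure for any continuous outcome, so there is none to reproduce. The 390 was derived for the binary outcome and is used here only as a head count.

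**Complete data, n per arm**
- Free T0 mean by arm (difference in change): V_free = 4(1 - rho)/n.
- Common T0 mean, or ANCOVA: V_common = 2(1 - rho^2)/n.
- Ratio V_common/V_free = (1 + rho)/2, so the variance is cut by (1 - rho)/2.

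**20% dropout after T0, likelihood model that keeps people with T0 only** (n = 195, m = 156)
- V_free = 2[(1 - rho^2)/m + (1 - rho)^2/n].
- V_common = 2(1 - rho^2)/m.
- With m = 0.8n the cut is 0.8(1 - rho)/[(1 + rho) + 0.8(1 - rho)]. At rho 0.5 this is 0.4/1.9 = 21%.

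| rho (assumed) | Cut in variance, complete data | Cut in variance, 20% dropout | Excess SE of free T0, complete data | Excess SE of free T0, 20% dropout |
|---|---|---|---|---|
| 0.3 | 35% | 30% | 24% | 20% |
| 0.5 | 25% | 21% | 15% | 12.5% |
| 0.7 | 15% | 12% | 8.5% | 7% |
| 0.8 | 10% | 8% | 5% | 4% |
| 0.9 | 5% | 4% | 3% | 2% |

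A direct calculation from the information matrices gives the same cuts, and adding T2 to the model with equal correlations leaves them unchanged.

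**Clustering in the intervention arm.** Adding ICC/16 to both variances, with 156 completers per arm and an assumed ICC of 0.05, gives cuts of 30%, 20% and 11% at rho 0.3, 0.5 and 0.7. With an ICC of 0.02 they are 33%, 23% and 13%.

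**Illustrative power.** Assume a 0.3 SD effect, rho 0.5, 156 completers per arm, no clustering and a normal approximation.
- Free T0: SE = sqrt(4 x 0.5/156) = 0.1132, and 0.3/0.1132 = 2.65. Power is 75.5% at two-sided 0.05.
- Common T0: SE = sqrt(2 x 0.75/156) = 0.0981, and 0.3/0.0981 = 3.06. Power is 86.4%.
- At 0.05/11 (critical value 2.84) the figures are 42.5% and 58.8%.
- If the free-T0 model also keeps people with T0 only, SE = sqrt(2[0.75/156 + 0.25/195]) = 0.1104. Its power is about 78% and 45%, against the same 86% and 59%.

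The 11 is the number of secondary rows in Table 2. The protocol does not define the Bonferroni family; one of those rows is medication and resource use, and some rows hold two instruments.

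**The case against.** The strongest reply is that the protocol nowhere says T0 is free by arm. A repeated-measures model with a common T0 mean also estimates a between-arm difference in change, so the quoted sentence fits the remedy proposed here. The exact parameterisation is the kind of detail an article leaves to an analysis plan. This stands: a reader might infer that the free-baseline model is fixed by the text, and it is not.

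The second reply is that the plan does provide for baseline imbalance. The baseline characteristics to be adjusted for could include T0 scale values, since the descriptive analysis covers health and psychosocial variables. This stands in part. The provision exists, but it does not name the T0 value, and it depends on differences seen in the data. The precision gain comes from using T0 every time, and a rule triggered by imbalance does not secure it.

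The third reply is that a 15 to 35% loss is not a property of this trial. That is correct. It is a variance figure that needs complete data and rho between 0.3 and 0.7. It falls to 12 to 30% with the stated dropout, and it is small if the scales are highly stable. Nor do the documents show that power on the secondary outcomes is low, because they give no power statement for them.

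What the replies leave untouched is that the article itself chooses change as the contrast and lists covariates without the outcome's own baseline.

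**Conclusion.** The point holds as a conditional matter of efficiency. If T0 is free by arm, which is the natural reading, a common-baseline model or ANCOVA cuts the variance on continuous outcomes by (1 - rho)/2 with complete data: 35%, 25% and 15% at assumed rho 0.3, 0.5 and 0.7. The cut is about 30%, 21% and 12% with the stated 20% dropout, and 4 to 10% at rho 0.8 to 0.9. These sizes rest on equal SDs and on a rho the documents do not supply; the power figures are illustrative only.

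A reader might go further and call the planned analysis biased or invalid. The documents do not support that: under randomisation the difference in mean change is unbiased and its test is valid. This is precision available for nothing, and not an error in the plan.

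**What to change.** For each continuous outcome, pre-specify one of the following, whatever baseline imbalance is observed:
- a repeated-measures model with the T0 mean constrained equal across arms (time and arm-by-post-baseline-time terms, no arm main effect, and the T0-T1 covariance estimated); or
- ANCOVA of T1 on T0.

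The first sits more naturally with the stated intention-to-treat set, because people with T0 only remain in the model. Keep the planned handling of group clustering, and name the adjusted difference as the reported effect.

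The cost is one model line. Every scale is already collected at T0. Trial status reports that no participant had completed the outcomes assessment when the article was submitted, so at that point the choice could still be made before any outcome data.

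### The good/bad primary outcome is modelled as a repeated linear response although eligibility leaves its baseline nearly constant; read most directly, with 20% dropout, the 5% test runs at about 8%

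*Protocol article*

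**What the plan says.** All references are to the Protocol article.

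- **Primary outcome.** The outcome is the first SF-36 item made binary, "considering good self-rated health if they answer (1) Excellent, (2) Very Good or (3) Good"; the two remaining categories count as bad. Table 2 in the same section lists SF-12 and the EQ-5D visual analog scale under primary outcomes.
- **Participants.** People are eligible if "they are community-dwelling aged 60 years or above and perceive their health as fair or poor". The item used is the outcome item: "Screening on self-rated health will be performed through the first item of the SF-36 questionnaire".
- **Randomisation and blinding.** "Participants who sign the informed consent will be scheduled for the baseline assessment", so the baseline interview is a separate occasion after screening.
- **Sample size.** 195 per arm, 20% dropout, and a target of a 10% increase in the prevalence of good health.
- **Data analysis.** Change from baseline to 3 months is assessed for primary and secondary outcomes alike by "comparing study arms (experimental and control group) with mixed linear models with repeated measures". No binary model is named. The intention-to-treat set is described as "including all randomized participants with a baseline assessment regardless of their permanence in the study". The one covariance statement is "A diagonal matrix design will be considered for the between-participants covariance matrices (covariance structure for random factors"; no residual structure is given. Correlation caused by group delivery is to be allowed for.

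**The concern.** Three choices fixed in the article fit together badly: a binary outcome, entry restricted to one of its two categories, and a model that treats the entry value as a first reading of the same response.

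At baseline (T0) nearly everyone is bad, so the response has almost no variance there. At 3 months (T1) it has the ordinary variance of a proportion. A linear mixed model with one residual variance averages the two and understates the variance at T1. Participants who drop out contribute only a baseline zero, and the model still counts that zero as information on the treatment contrast. The estimate is unharmed: with T0 equal in both arms, the contrast is simply the difference in T1 proportions. What is at stake is its standard error, and hence the confidence interval and the error rate of the confirmatory test.

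**Working it through.** **Plan's own figure.** Comparing 80% with 90% good at 80% power and one-sided 5% gives 157 per arm; 157/0.8 = 196.25, so 197 per arm (394 in total), close to the stated 195 (390). Two-sided, the same inputs give 199 and 199/0.8 = 248.75, so 249 per arm (498). That gap is a separate matter; only 195 per arm and 20% dropout are used below.

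**Inputs per arm.** n0 = 195 at T0 and n1 = 195 × 0.8 = 156 at T1. Let v be the variance of the 0/1 outcome at T1, and take the variance at T0 as 0.

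**Assumed because not stated.** Only T0 and T1 are in the model, with one common residual variance; data are missing completely at random; clustering is ignored.

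**Closed form.**

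1. T0 is constant, so its covariance with T1 is 0 and the random-intercept variance is estimated as 0.
2. Pooled residual variance = v × n1/(n0 + n1) = v × 156/351 = 0.444v.
3. Model variance of the change, per arm = 0.444v × (1/195 + 1/156) = v/195, that is v/n0.
4. True variance, per arm = v/156, that is v/n1.
5. Standard error ratio = sqrt(156/195) = sqrt(0.8) = 0.894.
6. Type I error = 2(1 − Φ(1.96 × 0.894)) = 2(1 − Φ(1.753)) = 7.96%.

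For illustration, assume 20% good at T1, so v = 0.16. The model reports a standard error of sqrt(2 × 0.16/195) = 0.0405. The correct value is sqrt(2 × 0.16/156) = 0.0453.

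**Other dropout rates, same formula.**

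| Dropout at T1 | SE ratio | Type I error |
|---|---|---|
| 0% | 1.000 | 5.0% |
| 10% | 0.949 | 6.3% |
| 20% | 0.894 | 8.0% |
| 30% | 0.837 | 10.1% |

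**Simulation under no effect, 195 per arm, 20% dropout.**

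- Two-wave model with common variance: 8.03% over 20,000 runs. Comparing T1 proportions alone in the same runs: 5.1%.
- Random-intercept model fitted by REML: 7.8% with 20% good at T1, 8.6% with 50% good. With no dropout: 4.7%.

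**Relaxing the assumptions.**

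- *Some answer good at the baseline interview.* With 5% or 10% good at T0, type I error is 7.5% or 5.8% when T0 and T1 are correlated. If T0 is independent of T1 it is 6.8% or 6.1%, and 5.1% in both cases with a separate variance at each time.
- *Follow-up at 9 months (T2) also in the model.* With 20% dropout it is 5.4% to 8.4% over the assumed T1–T2 correlations. With no dropout and low correlation it is 3.4%, which is conservative. A separate set of runs gave 3.2% to 5.9%.
- *Separate residual variance per time.* If T0 is exactly constant, its variance is driven to 0 and the likelihood is unbounded. This route works only if T0 varies somewhat.

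**The case against.** The strongest reply is that the 8% belongs to a model the article does not fully specify. Residual structure is commonly left to an analysis plan, outcomes are collected at three times, and the visit to which the 20% dropout applies is not given. The direction can also reverse when T2 enters. All of this stands. A reader might infer that the planned standard errors are simply wrong and the test invalid; the document does not support that. What remains is that the article names the baseline-to-3-month contrast and keeps everyone with a baseline, so the two-wave reading is the most direct one.

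Other stronger readings also fail:

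- **Wrong scale.** A linear model of 0/1 data estimates a risk difference, which is the scale of the 10-point target in the sample size section.
- **The diagonal matrix.** It is assigned to random factors and says nothing about the residual.
- **Covariance analysis on a constant.** The covariates named there are age, gender, education and socioeconomic level, not baseline self-rated health.
- **Baseline exactly constant.** Screening and baseline are separate interviews, so a few answers may change.

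Two further replies carry less weight. Bonferroni correction lowers the nominal level but leaves the standard error ratio unchanged. A linear mixed model does suit the visual analog scale in Table 2, but that does not help the dichotomised item that the text names as primary and the sample size is built on.

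**Conclusion.** The concern holds in conditional form. A repeated-measures linear model is planned for a binary primary outcome whose baseline is almost fixed by eligibility on the same item. With T0 and T1 only, a common residual variance, T0 all bad and 20% missing at T1, the standard error is about 11% too small and type I error is about 8% instead of 5%. The excess disappears with complete data, shrinks if some are good at baseline, and gives way to a range of about 3% to 8% if T2 is modelled. A confirmatory test whose error rate moves that far on unstated choices should be specified differently, particularly as the T0 rows add almost nothing.

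**What to change.** For the dichotomised primary outcome:

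- Compare the proportion good at T1 between arms, with T2 secondary, using a binary model (mixed logistic or GEE) or a risk difference with robust standard errors.
- Do not enter T0 as a repeated response. Use baseline fair versus poor only as a covariate.
- Adjust for primary care centre, the randomisation stratum, and keep the allowance for group delivery that is already planned.

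Keep linear mixed models for the continuous scales, including the EQ-5D visual analog scale, and reconcile Table 2 with the primary-outcome text.

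The cost is wording. No new data are needed, and the same software family can fit generalised mixed models and GEE. The Trial status section says that all participants had been included and none had completed the outcomes assessment, so on the article's own account the change could be specified before outcome data were available.
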